**B) REPORTING**

Non reactive specimens are reported as negative.

- Repeatedly reactive specimens are referred to VIDRL for confirmatory testing (HIV Western Blot) PRIOR to any report being released on the computer. A verbal report is given to [name] or one of the senior infectious diseases physicians.
- Repeatedly reactive specimens, which are also reactive on the HIV western blot, are reported as positive. Notify the pathology office when a positive or indeterminate report is verified.
- Pathology office staff should deliver the report to serology.
- Serology staff place the result in a sealed white envelope addressed to the referring doctor and marked **PRIVATE AND CONFIDENTIAL.**

## Other Serology

The following serological evaluations will be performed:

- Hepatitis B antigen - HBsAg plus confirmatory test if positive - Architect,  Anti-HBsAnti-HBc (total) - Architect, Anti-HBcIgM - Vidas (enzyme-linked fluorescence assay)
- HCV - Anti- HCV Architect, Murex Anti-HCV for positives (supplementary testing).
- HSV by ELISA, with PCR confirmation.

Information and counselling will be provided both pre- and post-testing.

## Urinalysis

A standard dipstick urinalysis will be performed including leukocytes.

In addition, a PCR will be performed for *N. gonorrhoeae* and *C. trachomatis.*

## Adverse Events

The Investigator and designated study personnel will monitor each subject for AEs during the study. All AEs reported between consent and final follow-up will be recorded in the CRF. The investigator or designee will ask the subject non-leading questions in an effort to detect AEs. Examples of such questions are:

*“How are you feeling?”*

Or

*“Since you were last asked, have you felt unwell or different from usual?”*

In addition, subjects should be encouraged to spontaneously report any unusual feelings or sensations. See Section 8. for full details on adverse experience reporting.

## Study Restrictions

## Dietary

There are no dietary restrictions during the study.

## Smoking

Participants must not smoke when visiting the study unit. There are no restrictions on smoking outside the unit.

## Confinement

Participants will be allowed to leave the clinical unit between study treatment administration and CV sampling, except when a time 0 sample or 1 hour sample is to be collected. If necessary, study participants may stay overnight at the clinic.

## Physical and Sexual Activity

The participants will be asked to refrain from intensive physical exercise and penile-vaginal and oral-vaginal intercourse between study treatment administration and CV sampling and for 24 hours before study treatment administration or before the pre-dose samples are taken. They will be allowed and encouraged to ambulate normally.

## Concomitant Medication

Vaginal preparations including lubricants will be not be allowed during the study. Lubricated condoms (non-N-9 containing) will be supplied to the participants. If the study participant develops a vaginal infection (other than an STI) after enrolment in to the study for which vaginally administered products are indicated and prescribed (i.e. to treat symptomatic candidiasis or symptomatic bacterial vaginosis), study visits will be suspended until at least 5 days after both the symptoms are completely resolved (as determined by the Principal Investigator), and the vaginally administered product is no longer being used.

## Use of Tampons and Sanitary Pads

Tampons are not to be inserted within 48 hours after application of study product, but may be used at any other time. If sanitary protection is required during the restricted period, then sanitary pads are to be used. Sanitary pads will be provided to study participants if requested, and panty liners to protect against gel leakage.

## Environmental Conditions

Except for the smoking restrictions outlined above, there are no restrictions on the environmental conditions under which CV samples and other study assessments are to be undertaken.

# SAFETY REPORTING

The reporting and documentation of AEs and clinically significant laboratory abnormalities or other assessments is an essential component of all clinical studies. Therefore, it is important that all investigational staff understand the requirements and responsibilities outlined below. It is the responsibility of the Investigator to ensure that all AEs and other clinically significant findings that occur during the conduct of a clinical study are documented and reported accurately.

AE(s) should be documented in terms of a medical diagnosis(ies), rather than signs and/or symptoms, where possible.

## Adverse Event Definitions

## Adverse Event (AE)

At each evaluation the investigator will determine whether any AEs have occurred by asking a non-leading question.

An AE includes any untoward medical occurrence in a patient or clinical investigational subject administered an investigational product (whether it is the experimental product or the control) and which does not necessarily have a causal relationship to the Study drug (whether it is the experimental product or the control).

The investigator will make a judgment regarding whether or not, in their opinion, the adverse event was related to the test drug. However, even if the investigator feels there is no relationship to the test drug, the AE should be reported. If any clinical adverse events have occurred they will be recorded on the AE report page of the CRF and their intensity will be graded.

AEs may include:

1. The significant worsening of the disease or symptoms of the disease under investigation following administration of investigational product/drug.
2. An intercurrent illnesses with an onset after administration of investigational product/drug.
3. Exacerbation (i.e., increase in frequency or intensity) of a pre-existing condition or event.

An AE does not include a/an:

1. Medical or surgical procedure: the condition that leads to the procedure is an AE.
2. Situations where an untoward medical occurrence has not occurred (e.g. hospitalization for cosmetic/elective surgery, social and/or convenience admissions).
3. Overdose of either study drug or concomitant medication that does not result in any signs or symptoms. (Note: Australian TGA requires Overdose reported as an SAE). If any signs or symptoms of an overdose present, then these will be recorded as an AE

## Serious Adverse Event (SAE)

An SAE is defined as any adverse drug experience occurring at any dose that results in any of the following outcomes:

- Results in deathb
- Is life-threateningc
- Requires in-patient hospitalization or prolongation of existing hospitalization
- Results in persistent or significant disability / incapacity
- Is a congenital anomaly / birth defect

a **Occurring at any dose**: Does not imply that the subject is receiving study drug at the time of the event. Dosing may have been given as treatment cycles or interrupted temporarily prior to the onset of the SAE, but may have contributed to the event.

b **Death**: Death is an outcome of an SAE, and not an SAE in itself. All deaths must be reported for volunteers on study and for deaths occurring within 30 days of last study drug dose or within 30 days of last study evaluation, whichever is longer, to Starpharma Regulatory and QA Department, who in turn will ensure immediate (with 24 hours) reporting to DAIDS Medical Officer, and reporting to TGA and FDA within the required timelines. The investigator should supply Starpharma and the IEC / IRB with any additional requested information as available (e.g. autopsy reports and terminal medical reports). Study participants will be asked to carry a card for 30 days post last study evaluation to identify that they have participated in a study, and provide contact details in the event of death.

c **Life-threatening**: The term “life-threatening” in the definition of “serious” refers to an event in which the subject was at immediate risk of death at the time of the event. It does not refer to an event which hypothetically might have caused death if it were more serious.

d **Hospitalization**: This is defined as the subject being hospitalized overnight, or the subject’s hospital stay being prolonged for at least an additional overnight stay. Hospital admissions for a pre-existing condition (e.g. elective surgery) or for normal disease management procedures (e.g. chemotherapy) will not be considered as serious. Complications that occur during hospitalizations are AEs. If a complication prolongs hospitalization, it is an SAE.

Important medical events that may not result in death, be life-threatening, or require hospitalization may be considered a serious adverse event when, based upon appropriate medical judgment, they may jeopardize the study participant and may require medical or surgical intervention to prevent one of the outcomes listed in this definition. Examples of such medical events include allergic bronchospasm requiring intensive treatment in an emergency room or at home, blood dyscrasias or convulsions that do not result in inpatient hospitalization, or the development of drug dependency or drug abuse.

.

## Unexpected Adverse Drug Reaction

Unexpected Adverse Drug Reaction is defined as an adverse reaction to study drug that is not identified in nature, severity or frequency in the IB or that is not expected from the characteristics of study drug.

## Reporting of an Adverse Event

## Adverse and/or Medically Significant Events

AE reporting will begin from first dose and will continue throughout the study until the Exit Evaluation.

## Serious Adverse Event

SAE reporting will begin from first dose and will continue until the Exit Evaluation.

**ANY** **SERIOUS ADVERSE EVENT** (INCLUDING DEATH) **DUE TO ANY CAUSE** WHICH OCCURS DURING THE COURSE OF THE INVESTIGATION, WHETHER OR NOT RELATED TO THE STUDY DRUG (INVESTIGATIONAL DRUG), **MUST BE REPORTED IMMEDIATELY** (within 24 hours of the investigator becoming aware of the event) TO STARPHARMA REGULATORY & QA DEPARTMENT AS FOLLOWS:

**Starpharma Switchboard Number: [contact]**

**Starpharma [contact]**

Telephone contact must be made with either the sponsor or study monitor in order to make an initial SAE report. Specific contact details and 24-hour contact details are available in the Study Procedures Manual.

Starpharma is responsible for reporting all SAEs to the DAIDS Medical Officer immediately upon being notified (within 24 hours).

The investigator (or delegate) will be requested to complete the Starpharma SAE form including as much information regarding the event that is available at the time of the initial report.

Investigators should not wait to receive additional information to fully document the event before notifying Starpharma of an SAE.

Prompt notification is essential so that legal requirements and ethical obligations to the subjects participating in the study can be met. A telephone report must be followed by a written report including copies of relevant medical records, autopsy reports and other relevant documents.

When reporting SAEs, the investigator should not include the name or address of the individual subject.

Minimum requirements for SAE reporting:

- Protocol number
- Centre name/ID
- Reporting investigator’s/physician’s name
- Subject initials, randomization number, age and sex
- Study drug dose and duration of treatment
- Condition treated (medical diagnosis, if known)
- Nature and severity of the SAE
- Relationship of SAE to Study drug
- Potentially confounding factors/concomitant medication*
- Action taken/outcome*

* Where action was taken or concomitant medication was administered, ensure that corresponding CRF pages have been completed.

The investigator must also:

- Report all SAEs to the reviewing IEC / IRB within the time-line specified by the reviewing body;
- Submit follow-up reports to Starpharma until the SAE has resolved or, in the case of permanent impairment, until the SAE stabilizes.

If the SAE is study drug related and unexpected, the SAE will be reported by Starpharma to the FDA, TGA and DAIDS Medical Officer within required timeframes (i.e. within 7 (fatal or life-threatening) or 15 (non-fatal or not life-threatening) calendar days of the event occurring and/or becoming aware of the event).

## Recording of an Adverse Event

- Adverse events All adverse events are to be recorded on the ‘Adverse Event’ pages within the subject’s CRF.
- Serious Adverse Events In addition to the ‘Adverse Event’ page, SAEs are to be recorded on the Starpharma Serious Adverse Event reporting form and then a copy is inserted into the study subject’s CRF.

At each clinical evaluation the investigator/delegate will determine whether any adverse events have occurred. The subject will be questioned in a non-leading way and no specific symptoms will be suggested. If known, the medical diagnosis of an AE should be recorded in preference to the listing of individual signs and symptoms.

The investigator/delegate will make a judgment regarding whether or not, in his/her opinion the study drug had any possible causal relationship to the Adverse Event. The investigator/delegate will evaluate any changes in laboratory values; make a determination as to whether or not the change is clinically important, and whether or not the changes were related to the study drug. However, even if the investigator/delegate feels there is no relationship to the study drug, the adverse event must be recorded in the CRF.

If any adverse events are present when a subject completes the study or when a subject is withdrawn from the study, the investigator/delegate should make every effort to follow-up the subject until the adverse event has resolved or stabilized. All follow-up information (and attempted follow-up contacts) should be documented in the subject’s medical records.

The severity of adverse events is graded in the first instance according to the Division of AIDS Female Genital Grading Table for Use in Micribocide Studies available on the RCC website at: http://rcc.tech-res.com. Those events not listed in the Female Genital Grading Table will be graded according to The Division of AIDS Table for Grading the Severity of Adult and Pediatric Adverse Events (DAIDS AE Grading Table), Version 1.0, December, 2004, also available at http://rcc.tech-res.com.

Those adverse events not covered within either of the above toxicity tables will be graded as follows:

***Grade 1: Mild*** An AE that causes no or minimal interference with usual social and functional activities.

***Grade 2: Moderate*** An AE that causes greater than minimal interference with usual social and functional activities.

***Grade 3: Severe*** An AE that causes inability to perform usual social and functional activities.

***Grade 4: Life Threatening*** An AE that causes inability to perform basic self-care functions or medical or operative intervention is indicated to prevent permanent impairment, persistent disability or death.

***Grade 5: Death*** An AE that results in death.

It should be noted that an AE that is considered to be “severe” may not necessarily be considered to be “serious” or of major medical significance.

The relationship to study drug therapy should be assessed using the following definitions:

***Not Related*** The adverse event is clearly explained by another cause not related to the study agent.

***Probably Not Related*** A potential relationship between study agent and the adverse event could exist (i.e. the possibility cannot be excluded), but the adverse event is most likely explained by causes other than the study agent.

***Possibly Related*** The adverse event and administration of study agent are reasonably related in time, and the adverse event can be explained equally well by causes other than the study agent.

***Probably Related*** The adverse event and administration of study agent are reasonably related in time, and the adverse event is more likely explained by study agent than other causes.

***Definitely Related*** The adverse event and administration of study agent are related in time, and a direct association can be demonstrated.

It should be emphasized that ineffective treatment should not be considered as causally related in the context of AE reporting.

These criteria in addition to good clinical judgment should be used as a guide for determining the causal assessment.

The degree of certainty with which an adverse event is attributed to study drug/product treatment or alternative cause, (e.g. natural history of the underlying diseases, concomitant therapy, etc) will be determined by how well the event can be understood in terms of:

- Known pharmacology of the product.
- Reaction of a similar nature previously observed with similar products/drugs.
- The event having often been reported in literature for similar products as product related.
- The event being related by time to product/drug administration/ termination, product/drug withdrawal, or reproduced on rechallenge.

## Clinical Laboratory Abnormalities and Other Abnormal Assessments as Adverse Events or Serious Adverse Events

Laboratory abnormalities deemed not clinically significant and not considered an AE according to the DAIDS toxicity tables are usually not recorded as AEs or SAEs. However, all abnormal laboratory findings (e.g. clinical chemistry, haematology, urinalysis) or other abnormal assessments (e.g. vital signs) that meet the definition (or cause signs and symptoms that meet the definition) of an AE (or SAE) must be reported as outlined above.

## Toxicity Management

AEs and laboratory abnormalities will be graded as outlined in Section 8 .

For the purpose of monitoring toxicities, the baseline value is defined as the last value prior to the administration of the first dose of study medication. All management is based on changes from this value.

All grade 2 or higher laboratory abnormalities should be confirmed by repeat testing as soon as possible, preferably within 3 calendar days of receipt of results prior to dose interruption or discontinuation, unless such a delay is not consistent with good medical practice.

In response to AEs reported by study participants and/or observed upon exam by study staff, the study site investigator or designee will recommend either continuation or holding study gel use consistent with the criteria in Section 16.3. Study gel use also will be held or discontinued in the event of an expedited adverse event (EAE) that is judged by the site Investigator or designee to have a potential causal relationship with study product.

Unless the participant withdraws consent, she will remain in the study to complete the safety evaluations (unless clinically contraindicated according to Section 16.3).

Study participants who develop an RTI (i.e. bacterial vaginosis (BV) or candidiasis) requiring treatment whilst on study will not be withdrawn, but study product will be suspended until symptoms have resolved and treatment is completed as outlined in Section 7.4.5. However, study participants who develop an STI during the study period are to be withdrawn from the study.

## Pausing / Stopping Rules

The study will be paused if:

- 2 or more participants report a grade 3 or higher genital AE, considered to be related to study medication or
- Ulceration considered to be related to study medication and with no clear explaination is seen in 2 or more participants or
- study product is discontinued in 3 or more participants due to genital events considered to be related to study medication

In the event that a decision is taken to pause the study according to the above criteria, a full review will take place of all the AE data for all subjects by the Principal Investigator, DAIDS Medical Officer, Medical Monitor and Starpharma. The ethics committee and DAIDS are to be immediately notified of this decision. By reviewing the full data along with the data emerging from the ongoing study(ies) and that from existing studies, the team will come to a decision based on their judgement and expertise as to the next course of action, which could be:

1. To restart the study with no amendment to the protocol
2. To restart the study after implementation of a protocol amendment.
3. To place the study on clinical hold pending the emergence of further data.
4. To terminate the study

The ethics committee, TGA, FDA, and DAIDS are to be notified of any protocol amendment, study hold, or termination of the study according to applicable regulations as outlined in Sections 9.6 and 11.

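### The mandatory pause rule counts only genital events or ulceration in two or three women, so one related fatal or life-threatening SAE requires neither a study pause nor the joint review

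*Protocol*

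**What the plan says.** The Pausing / Stopping Rules section (in section 8, after Toxicity Management) states that the study will be paused if one of three conditions is met:

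- Trigger 1 counts severe local events and needs two women: "2 or more participants report a grade 3 or higher genital AE, considered to be related to study medication or".
- Trigger 2 needs two women with related ulcers that have no evident other cause.
- Trigger 3 counts women taken off the gel and needs three: "study product is discontinued in 3 or more participants due to genital events considered to be related to study medication".

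The review is tied to these conditions: "In the event that a decision is taken to pause the study according to the above criteria, a full review will take place". It is carried out by the principal investigator, the DAIDS Medical Officer, the medical monitor and the sponsor, with immediate notice to the ethics committee and DAIDS. It has four possible outcomes, the mildest being "To restart the study with no amendment to the protocol".

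Other provisions bear on a serious event:

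- Section 9.6 allows the investigator, sponsor, DAIDS, FDA or TGA to terminate the study on the number or severity of AEs.
- Section 12.12 lets the sponsor suspend or discontinue the study.
- Section 8.2.2 requires SAEs to reach the sponsor within 24 hours, and the sponsor then to inform the DAIDS Medical Officer within 24 hours.
- Section 8.7 sets expedited reporting at the Intensive Level, with simultaneous notice to the DAIDS Medical Officer.
- Sections 8.5 and 16.3 hold or stop gel after a potentially related expedited event.

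Systemic safety is part of the secondary objective (section 3.2), and systemic toxicity is a safety endpoint in the synopsis.

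**The concern.** The binding rule is ordered the wrong way round. Two related grade 3 genital events require a pause and a four-party review. One related death or life-threatening event requires neither. The rule also has no limb for systemic events, although systemic safety is a stated objective.

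The participant-level and study-level rules do not connect either. Under section 16.3 a grade 4 expedited event with even a remote link to the gel or applicator permanently ends dosing for that woman. If the event is not genital, her discontinuation does not count towards the third pause trigger.

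At stake is whether the remaining healthy volunteers, who gain no direct benefit (section 2.4), go on being dosed while the event is assessed. As written, that rests on someone choosing to intervene.

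**Working it through.** The protocol gives no operating characteristics for the pause rule, so there is no stated figure to reproduce. The check is mainly logical.

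**Step 1. Test events against the three triggers.**

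| Event, judged related | Trigger 1 (grade 3+ genital, ≥2 women) | Trigger 2 (unexplained ulceration, ≥2 women) | Trigger 3 (stopped for genital events, ≥3 women) | Pause required |
|---|---|---|---|---|
| One fatal or life-threatening non-genital SAE | No: not genital | No | No | No |
| One fatal or life-threatening genital SAE | No: 1 < 2 | No: at most 1 < 2 | No: 1 < 3 | No |
| Several severe non-genital, non-ulcer events | No: not genital | No | No: not genital | No |
| Two grade 3 genital AEs in two women | Yes | – | – | Yes |

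Because the review depends on a pause under these criteria, the first three rows do not require it either.

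**Step 2. Look for another mandatory study-level rule.** Section 9.6 is permissive and section 12.12 reserves a right. Neither sets a trigger or calls for the joint review. Sections 8.2.2 and 8.7 require notification only. Sections 8.5 and 16.3, read in context, act on the individual woman. Safety boards and an independent safety monitor appear in the abbreviation list, but the visible text gives them no role.

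**Step 3. Doses exposed to the gap.** Inputs: 12 women (section 5.2), 5 doses each, at least 5 days apart (synopsis).

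- Planned doses: 12 × 5 = 60.
- Event after the first dose in the study: up to 11 × 5 = 55 doses remain in the other women.
- Event when each of the others has had one dose: up to 11 × 4 = 44.
- Event late in the study: few or none.

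Replacement of drop-outs is ignored. These are upper limits on dosing without a mandated pause; they do not predict that dosing would continue.

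**Step 4. Timing.** FDA and TGA are due a report of a related, unexpected fatal or life-threatening SAE within 7 calendar days (section 8.2.2). Doses may be 5 days apart, so another woman could be dosed again before that report is due.

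**Step 5. How often would a two-woman threshold respond?** This is illustration only, because the protocol gives no event rates. Let X be the number of the 12 women with such an event, binomial with assumed per-woman rate p:

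- P(X ≥ 1) = 1 − (1 − p)^12
- P(X = 1) = 12p(1 − p)^11
- P(X ≥ 2) = P(X ≥ 1) − P(X = 1)

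| Assumed p | P(X ≥ 1) | P(X ≥ 2) | P(X = 1 given X ≥ 1) |
|---|---|---|---|
| 0.1% | 1.2% | 0.01% | 99.5% |
| 0.5% | 5.8% | 0.16% | 97.3% |
| 1% | 11.4% | 0.62% | 94.6% |

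For p = 1%: 1 − 0.99^12 = 0.1136; 12 × 0.01 × 0.99^11 = 0.1074; 0.1074 / 0.1136 = 0.946 before rounding of the inputs. The last column falls as p rises, so 94.6% is the minimum for any rate up to 1%.

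**The case against.** The strongest reply is that the protocol is not silent. Five parties may terminate on severity alone, the sponsor may suspend freely, and the people able to act hear of an SAE within a day or two. The genital focus is also reasoned: section 6.9 lists almost wholly local effects and reports no systemic absorption in animals or humans. Some background was removed as proprietary and may hold further rationale. The rule's own follow-on sentence speaks of a decision to pause, so even the listed triggers may be less automatic than they look. Finally, the assumed event rates have no basis in the protocol.

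Much of this stands. It limits the gap to the lack of an automatic trigger: authority to stop and prompt information are both present. It makes the event unlikely. The probabilities in step 5 describe any rare event among 12 people and are not evidence about this gel.

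It does not remove the gap. Absence of absorption bears on likelihood and does not say what must happen if the event occurs; a life-threatening genital event in one woman escapes the rule as well. Any reading that softens the listed triggers leaves the unlisted event with still less. Missing background cannot change what the three triggers cover.

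**Conclusion.** The concern holds. Followed to the letter, the only mandatory pause rule does not respond to one related fatal or life-threatening SAE, or to any number of severe related events that are neither genital nor ulcerative, and the joint review is then not required. Between 55 planned doses in the other 11 women and none would proceed without a mandated pause, depending on when the event falls.

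The logical result needs no assumption beyond the usual reading that sections 8.5 and 16.3 govern the individual participant. The probabilities rest wholly on assumed rates and only show that a two-woman threshold suits such an event poorly.

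This should be corrected. The likelihood is low and other controls exist, so it is a gap in participant protection and does not affect the validity of the primary analysis.

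**What to change.** Add one trigger to the Pausing / Stopping Rules: *any one SAE judged related to study medication that is fatal, or life-threatening as section 8.1.2 defines it*. The existing review and its four outcomes then apply unchanged.

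Use the section 8.1.2 definition, under which life-threatening "refers to an event in which the subject was at immediate risk of death at the time of the event", and not grade 4 or 5. Section 8.3 applies the DAIDS tables first and its own verbal scale only last ("Those adverse events not covered within either of the above toxicity tables will be graded as follows"). Section 8.5 extends grading beyond clinical events ("AEs and laboratory abnormalities will be graded as outlined in Section 8"). A grade-based trigger could therefore fire on a single laboratory value.

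Optional and secondary: let the first trigger count related clinical AEs of grade 3 or higher in any body system, still in two or more women. Limit it to clinical events, because scheduled bloods are taken only at screening and at follow-up, at least a week after a woman's last dose, where a raised value is hard to tie to dosing.

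The new trigger inherits a looseness already in the existing three: none says which of the five causality categories in section 8.3 count as related. The same amendment could settle that.

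The cost is one bullet, plus a few words if the optional change is taken, and the approvals that section 11.3 requires for an amendment. No new committee, visit or test is needed. The downside is a slightly higher chance of an unnecessary pause, which the first review outcome already handles by allowing a restart without amendment.
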